# Single blind randomized Phase III trial to investigate the benefit of a focal lesion ablative microboost in prostate cancer (FLAME-trial): study protocol for a randomized controlled trial

**DOI:** 10.1186/1745-6215-12-255

**Published:** 2011-12-05

**Keywords:** microboost, prostate cancer, external beam radiotherapy, FLAME-trial

## Abstract

**Background:**

The treatment results of external beam radiotherapy for intermediate and high risk prostate cancer patients are insufficient with five-year biochemical relapse rates of approximately 35%. Several randomized trials have shown that dose escalation to the entire prostate improves biochemical disease free survival. However, further dose escalation to the whole gland is limited due to an unacceptable high risk of acute and late toxicity. Moreover, local recurrences often originate at the location of the macroscopic tumor, so boosting the radiation dose at the macroscopic tumor within the prostate might increase local control. A reduction of distant metastases and improved survival can be expected by reducing local failure. The aim of this study is to investigate the benefit of an ablative microboost to the macroscopic tumor within the prostate in patients treated with external beam radiotherapy for prostate cancer.

**Methods/Design:**

The FLAME-trial (**F**ocal **L**esion **A**blative **M**icroboost in prostat**E **cancer) is a single blind randomized controlled phase III trial. We aim to include 566 patients (283 per treatment arm) with intermediate or high risk adenocarcinoma of the prostate who are scheduled for external beam radiotherapy using fiducial markers for position verification. With this number of patients, the expected increase in five-year freedom from biochemical failure rate of 10% can be detected with a power of 80%. Patients allocated to the standard arm receive a dose of 77 Gy in 35 fractions to the entire prostate and patients in the experimental arm receive 77 Gy to the entire prostate and an additional integrated microboost to the macroscopic tumor of 95 Gy in 35 fractions. The secondary outcome measures include treatment-related toxicity, quality of life and disease-specific survival. Furthermore, by localizing the recurrent tumors within the prostate during follow-up and correlating this with the delivered dose, we can obtain accurate dose-effect information for both the macroscopic tumor and subclinical disease in prostate cancer. The rationale, study design and the first 50 patients included are described.

**Trial registration:**

This study is registered at ClinicalTrials.gov: NCT01168479

## Background

Localised prostate cancer can be treated by radical prostatectomy, brachytherapy or external beam radiotherapy. For low risk tumors the results of external beam radiotherapy are comparable to radical prostatectomy and brachytherapy with freedom from biochemical failure rates approximating 95% after 5- to 10-year follow-up [1]. For high risk patients, external beam radiotherapy is preferred. The outcome for intermediate and high risk patients is insufficient with freedom from biochemical failure ranging between 60% and 75% after 5- to 10-years follow-up [2-4].

Several randomized trials have proven that dose escalation in external beam radiotherapy improves the biochemical disease free survival [2,4-6]. Pollack *et al*. [2] compared the efficacy of 70 Gy versus 78 Gy on 305 patients with stage T1-3 prostate cancer. For patients with a pretreatment PSA > 10 ng/mL the freedom from biochemical failure rate at five year was 43% versus 62% respectively, in favor of the higher dose group. The randomized trial from Peeters *et al*. [4] compared 68 Gy versus 78 Gy on 669 patients with stage T1-4 prostate cancer. Five-year freedom from failure rate was significantly improved from 54% to 64%. Further increase in dose is considered to improve the treatment results even further [2,4,7]. Dose response models suggest that tumor areas with severe hypoxia will need very high (ablative) doses [8]. Moreover, local recurrences often occur at the site of the primary macroscopic tumor [9,10], so boosting the radiation dose to the macroscopic tumor might increase the local control. An improvement in distant metastases and survival can be expected by reducing local failure, due to the fact that local failure is associated with distant metastases and mortality [11-13].

Dose escalation to the entire prostate is not considered feasible by reason of unacceptable toxicity risks. This problem can be overcome by partial boosting strategies. In this way, the macroscopic tumor can be irradiated to a very high dose, while the dose constraints to the rectum and bladder can be maintained [14,15]. This approach is being used to deliver a microboost to the dominant tumor region in a number of pilot studies [16-19]. The dose to the macroscopic tumor is increasingly escalated. The highest dose was delivered in a feasibility study by Singh *et al*. [20] who treated 3 patients with an ablative dose of 95 Gy to the macroscopic tumor within the prostate with no severe toxicity (≥ grade 3).

To investigate the benefit of an ablative microboost to the macroscopic tumor within the prostate, we started a randomized controlled trial (the FLAME-trial: **F**ocal **L**esion **A**blative **M**icroboost in prostat**E **cancer, clinical trials: study protocol number NCT01168479). The purpose of this trial is to assess whether a dose escalation to the macroscopic tumor increases the five-year freedom from biochemical failure rate. Furthermore, we will assess the influence of this dose escalation on treatment-related toxicity, quality of life (QoL) and disease-specific survival.

## Methods/Design

### Study design

The FLAME-trial is a multicenter randomized controlled trial. Patients are recruited during the intake consultation at the Department of Radiation Oncology in one of the participating centers. After giving informed consent, patients are randomized either to the standard arm or to the experimental arm. Patients in the standard arm receive radiotherapy according to the current standard [4], namely 77 Gy in 35 fractions of 2.2 Gy to the whole prostate. Patients in the experimental arm receive an additional integrated microboost to the macroscopic tumor to a total dose of 95 Gy in 2.7 Gy fractions.

To ensure unbiased assessment of QoL measurements, the patients are blinded to the actual treatment given (receiving an ablative microboost or not). The treating physician needs to be informed about the actual treatment, to be able to judge the treatment plans. This is unlikely to influence the assessment of the objective primary endpoint of the trial.

### Patients

Men with histological proven intermediate or high risk adenocarcinoma of the prostate, who will receive external beam radiotherapy using optimal position verification with implanted fiducial gold markers, are eligible for the study. Intermediate or high risk is defined according to the currently internationally accepted criteria from Ash *et al*. [21]. Intermediate risk is defined as patients having one factor of stage T2b-c, or Gleason score = 7, or initial prostate-specific antigen (iPSA) = 10-20 ng/mL. Patients having more than one of these factors or having stage T3, or Gleason score >7, or iPSA > 20 ng/mL are defined as high risk. Patients with low risk tumors are not included in this study, because the treatment outcome for this group is already excellent with a 10-year prostate cancer-specific survival approximating 95% [1].

Exclusion criteria are: previous pelvic irradiation, previous prostatectomy, World Health Organization (WHO) performance score > 2 [22] (= symptomatic, >50% during the day in bed, but not bedbound (score 3) or bedbound (score 4)), International Prostate Symptom Score (IPSS) ≥ 20, transurethral resection of the prostate (TURP) within 3 months from start of the treatment, general contraindications for MRI (i.e. cardiac pacemaker, metal implants or history of severe allergic reaction after administration of contrast agent) or the use of anti-coagulants that cannot be discontinued for the gold markers implantation.

The study protocol is approved by the Medical Ethical Committees of the participating hospitals. Written informed consent will be obtained from all patients.

### Randomization

Randomization is performed by an independent trial center. If a patient meets the inclusion criteria and has provided informed consent, the physician contacts the trial center. To prevent randomly occurring differences in important prognostic factors across the two randomized groups, the randomization is stratified by TURP, hormonal treatment and by centre. A TURP prior to radiotherapy is associated with significantly more late genitourinary toxicity [23,24]. The likely mechanism of increased late toxicity is related to the relative devascularisation of the urethra after TURP and the decreased capability of the mucosa to repair sublethal damage after radiotherapy [24]. Hormonal treatment is a prognostic unfavorable factor for late genitourinary side effects [23,25] and erectile impotence [26-28]. Furthermore, a protective effect for hormonal treatment is reported for acute gastrointestinal side effects [23,29,30]. To prevent small numbers of patients in a particular hospital from all receiving, by chance, the same treatment, the hospital is chosen as one of the factors for stratified randomization as well.

### Time schedule

Between October 2009 and October 2010, the first 50 patients were included at the Department of Radiation Oncology of the University Medical Center Utrecht. Based on this accrual and the fact that other participating centers recently started to include patients as well, we expect that the accrual will be completed within 5 years from start.

### Radiotherapy

To minimize the positioning errors during treatment all patients are treated with an online position verification protocol using implanted fiducial gold markers [14,31,32]. Radiotherapy will be delivered with advanced radiotherapy techniques to be able to create adequate dose distributions.

A mean dose of 77 Gy in 35 fraction of 2.2 Gy is prescribed to the entire prostate gland [33,34]. The dose in the part of the PTV overlapping the rectum and bladder is limited to keep the risk of severe gastrointestinal and genitourinary toxicity acceptable.

To provide an accurate delineation of the prostate gland with respect to the surrounding tissues [35,36], the prostate is delineated on a computed tomography (CT) scan combined with a registered magnetic resonance imaging (MRI) scan. The rectum is contoured from the anus or ischial tuberosities to the rectosigmoid flexure or sacroiliac joints. The bladder is completely outlined from the bladder neck to the dome.

The precise execution of the radiotherapy treatment can differ in each participation center, but the treatment will always meet the above mentioned criteria.

### Intervention

Patients randomized to the experimental arm are treated with the current standard of 77 Gy to the whole prostate and in addition receive an integrated microboost to the macroscopic tumor to reach a total dose of 95 Gy in 35 fractions of 2.7 Gy. To delineate the macroscopic tumor within the prostate, different MR imaging techniques are used. In addition to an anatomic T2 weighted sequence, a combination of the following functional imaging modalities can be used [37,38]. Dynamic contrast-enhanced (DCE)-MRI gives a characterization of the tissue vasculature [39]. With this technique it is possible to detect areas with macroscopic tumor, because tumors tend to contain higher density of leaky blood vessels. With diffusion-weighted imaging (DWI)-MRI the mobility of water molecules is measured [40]. Tumor tissue can be identified on DWI-MRI, because in tumor the extracellular volume is reduced, leading to reduced water diffusion in tumor tissue. MR spectroscopic imaging (MRS) provides metabolic information with cancer regions showing higher choline and lower citrate levels [41].

### Primary endpoint

To evaluate whether the addition of an ablative microboost to the macroscopic tumor within the prostate increases the five-year freedom from biochemical failure rate compared to the current standard of care. Biochemical failure is defined according to the Phoenix definition as a PSA rise of 2 ng/mL above the nadir PSA level [42]. The PSA level will be measured every six months until 10 years after treatment.

### Secondary endpoints

Secondary endpoints are treatment-related toxicity, QoL and disease-specific survival. Treatment-related toxicity is measured by the Common Toxicity Criteria for adverse events version 3.0 (CTCAE) [43]. The following adverse events are scored: urinary frequency/urgency, urinary retention, bladder spasms, urinary incontinence, genitourinary hemorrhage, dysuria, rectal or perirectal pain, proctitis, diarrhea, flatulence hemorrhoids, anal incontinence, erectile dysfunction. The physician in attendance scores the complaints before treatment, acute toxicity (weekly during treatment and 4 weeks after treatment) and late toxicity (every six months until 10 years after treatment). All symptoms are registered even if they occur only on one single occasion. Grade > 2 is considered severe toxicity.General health-related QoL is measured using the RAND-36 generic health survey [44], cancer-specific QoL using the European Organization for Research and Treatment of Cancer (EORTC) core questionnaire (QLQ-C30) [45], and the prostate tumor-specific QoL using the EORTC prostate cancer module (QLQ-PR25) [46]. The disease- and treatment-related side effects are only a component of health-related quality of life [47]. To address the components of overall well-being, a general instrument is used in addition to the disease-specific questionnaires [48-50]. The RAND-36 assesses physical and social functioning, physical and emotional role restriction, mental health, vitality, pain, general health and change in health. The EORTC QLQ-C30 contains five functional scales, three symptoms scales, a global QoL scale and six single-items. The EORTC QLQ-PR25 assesses urinary, bowel and sexual symptoms and functioning, and the side effects of hormonal treatment. The first questionnaire is handed over to the patient one week before treatment at the Department of Radiation Oncology and the next questionnaires are sent to the patient every six months until 10 years after the completion of the treatment. It is important to measure QoL every 6 months after treatment, to be able to determine the point in time at which the QoL changes, for example due to side-effects after treatment.

For disease-specific survival, death with metastases is considered a death caused by the disease.

### Safety

An independent data safety monitoring board (DSMB) will evaluate the toxicity and clinical outcome. The DSMB receives an update of the toxicity in total and per treatment arm every 3 months. Serious toxicity, defined as any acute or late toxicity requiring surgical intervention, any grade 4 toxicity, and any not-transient (duration >6 months) late toxicities grade 3, will immediately be reported to the DSMB. An overview of the percentage of biochemical recurrences per treatment arm together with the evaluated number of patients per arm will be sent to the DSMB yearly as well as a statistical comparison of the incidence of serious and less serious toxicities in the two arms. The DSMB decides on stopping or continuing the trial. Exact rules cannot be specified in advance, but an increase in the incidence of toxicity (grade 3-4) with 5% or a smaller, but statistically significant increase, are among the reasons to consider stopping the trial. The DSMB can decide to prematurely stop the trial in case the improvement in the experimental arm is higher than anticipated in the trial design.

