### Sample size considerations

The statistical power of the study was calculated for the primary endpoint (five-year freedom from biochemical failure). Based on data of two randomized clinical trials [2,51] reporting the treatment results of patients treated with a radiation dose equal to the dose of the standard arm of our trial, we expect that the five-year freedom from biochemical failure of the standard arm will be approximately 64%. We expect that an additional ablative microboost to the macroscopic tumor will increase this number with at least 10%. A one-sided log rank survival power analysis shows that the length of follow-up after accrual of the last patient should be 3.5 years to detect a difference of 10% (64% and 74% free from biochemical failure after 5 years, in the control arm and experimental arm, respectively) with a power of 80% at a one-sided 5% significance level. This is under the assumption that the patients enter the study during an accrual period of 5 years, 50% of the enrollment is complete when 70% of the accrual time has past and that 20% of the patients in both arms are lost to follow-up during the follow-up period of 5 years. The reason to choose a one sided p-value is that, although extremely improbable, an increase in biochemical failure in the experimental arm would lead to the same action as no difference at all between the two treatment arms. This is because the experimental treatment will only be implemented if it is significantly better than the usual treatment, due to the increased toxicity risk in the experimental arm.

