### Data analysis

All analysis will be performed according to the intention-to-treat principle. Cox proportional hazards regression will be used to analyze differences in biochemical failure and disease-specific survival between the two treatment arms. Survival curves will be estimated by the Kaplan-Meier technique. Differences between both groups in the incidence of acute side-effects will be tested with the Chi square test. The incidence of late toxicity will be analyzed actuarially with the Kaplan-Meier method, the log rank test and Cox regression analysis. To analyze differences in QoL between the two treatment groups over the time points, a general linear model repeated-measures analysis of covariance will be performed [52]. A change of 10% (or in general, 0.5 standard deviation) of the scale width is perceptible to patients as a meaningful change [53]. Because of the multiple comparisons for the QoL items, the p-value is set at a conservative 0.01 for determining statistical significance [54]. For all other analyses, which do not include the QoL measures, a p-value of < 0.05 is considered statistically significant.

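### The efficacy stopping provision has no statistical boundary, so the one-sided 5% error rate of the primary comparison is not controlled

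*Protocol article*

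**What the plan says.** In Safety, the board is sent yearly "An overview of the percentage of biochemical recurrences per treatment arm", with the numbers evaluated. The statistical comparison mentioned in the same sentence concerns toxicities. The board decides whether the trial continues. The section says "Exact rules cannot be specified in advance", goes on to give toxicity examples, and then adds for efficacy that the board "can decide to prematurely stop the trial in case the improvement in the experimental arm is higher than anticipated" at the planning stage.

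Sample size considerations plans one log-rank comparison of 64% against 74% free from biochemical failure at five years, "with a power of 80% at a one-sided 5% significance level". It mentions no interim efficacy analysis. It justifies the one-sided test by saying that the boost will be adopted only on statistically significant superiority.

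Data analysis keeps an unadjusted final threshold: "For all other analyses, which do not include the QoL measures, a p-value of < 0.05 is considered statistically significant".

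**The concern.** The only stated criterion for an efficacy stop is that the observed improvement exceeds the planned one. That is a point estimate with no measure of its uncertainty. At early reviews there are few failures, so chance alone often produces an apparent effect larger than planned. A trial that can end on such an observation, and otherwise goes on to a full 5% test, has more than one route to a positive conclusion, and nothing offsets the extra routes.

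Two further problems follow. A stop that is conditional on a large estimate selects overestimates. And the planned effect is a five-year difference, whereas the board is sent a percentage of recurrences among patients with very different follow-up, so the two are not on the same scale.

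**Working it through.** **1. The stated design reproduces as a single look.** Inputs from the abstract and Sample size considerations: 283 per arm, 64% v 74% at 5 years, 5-year accrual with half enrolled at 70% of that time (3.5 years), 3.5 years of further follow-up, 20% lost per 5 years.

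- Hazard ratio under exponential failure: ln 0.74 / ln 0.64 = 0.3011 / 0.4463 = 0.675; log hazard ratio 0.3935 in size.
- Events needed (Schoenfeld): 4 × (1.645 + 0.842)² / 0.3935² = 4 × 6.18 / 0.1548 = 160. Freedman's formula gives 164.
- Expected events at 8.5 years, with exponential loss and an exponentially rising entry curve: about 163.
- Power: Φ(√162.6 / 2 × 0.3935 − 1.645) = Φ(0.864) = 80.6%.

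The stated 80% is thus used up by one final test. Nothing was set aside for interim looks.

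**2. Little information exists early.** On the same assumptions, expected failures at years 1 to 5 are about 2, 7, 18, 36 and 64, of about 163 finally.

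**3. The percentage scale does not match the planned effect.**

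- Year 1. The article reports 27 standard and 23 experimental patients among the first 50. Suppose three recurrences in the standard arm and none in the other: 3/27 = 11.1 points, above the planned 10. The one-sided exact probability is C(27,3)/C(50,3) = 2,925/19,600 = 0.15.
- Year 4. About 361 patients are enrolled with about 36 failures, or 10% overall. A 10-point difference would need roughly 15% v 5%, a threefold ratio and far more than planned.

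The same wording is lax at one review and very strict at another.

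**4. Overall false-positive rate under no effect.** Both arms 64% at 5 years, yearly looks up to year 8, final one-sided 5% test at 8.5 years, 30,000 simulated trials. A false positive is an efficacy stop or a significant final test.

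| Reading of the trigger | Looks from year 1 | Later first look |
|---|---|---|
| Crude difference above 10 points | 10.6% | 7.4% (yr 2), 5.9% (yr 3), 5.3% (yr 4) |
| 5-year Kaplan-Meier difference above 10 points | not estimable | 15% (yr 6); 7% if p<0.05 also required |
| Log-rank one-sided p<0.05 | 20% | 15% (yr 3), 11% (yr 5) |
| Hazard ratio below 0.675, no p-value | 55% | 40% (yr 2), 25% (yr 3), 15% (yr 4), 8% (yr 5), 5-6% (yr 6-7) |
| Hazard ratio below 0.675 and p<0.05 | 18% | 13% (yr 3), 8% (yr 5) |

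A separate Brownian-motion calculation gives 21% for the log-rank row from year 1, and 5.0% for the final test alone.

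**5. Bias.** If the true difference is 10 points or less, every estimate that satisfies the trigger exceeds the truth by construction.

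**6. Conservative boundaries.** Brownian motion, information = events/4, drift 0 or 0.3935, one million runs, looks at years 1-8 and 8.5.

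- p<0.001 at each interim, final test at 5%: overall error 5.3%, power 81%, and a 31% chance of stopping early under the planned effect. Unadjusted 0.05 looks would stop early in 86%.
- O'Brien-Fleming-type: overall error 5.0%, final critical value 1.78 (nominal one-sided p about 0.037), power 79%.

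**The case against.** The strongest reply has four parts.

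*The article is condensed, and a boundary may sit in a board charter or the full protocol.* That would excuse silence. Here the article states a trigger, and the trigger is an effect size without a significance condition. The remark that exact rules cannot be given leads into toxicity, so it does not by itself rule out an efficacy boundary elsewhere. The point does not depend on it.

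*The stop is discretionary, and a stop is not a claim of efficacy.* This stands in part. An independent board that also weighs toxicity may decline to stop, and the adoption condition in the sample size section could be applied afterwards. Requiring p<0.05 as well lowers most of the rates. But the board's criterion does not include that condition, so the two passages pull apart. Even with it added, repeated looks without adjustment can still exceed 5%.

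*The planned improvement is a five-year quantity, estimable only from about year 6.* This is a fair reading, and it weakens the early-look scenarios, including the 55%. It still gives about 15% without a significance condition.

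*The percentages need not be crude.* Correct: the article does not say how follow-up is handled, nor that the board sees nothing else. The yearly timing of a stop is likewise inferred from when efficacy data arrive.

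A reader might infer that the provision raises the error to some definite range, such as 10-40%. The documents do not support that. With neither statistic nor first look defined, the readings tried here run from almost no inflation to more than 50%, and the one closest to the data described, a crude difference, lies at the low end.

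**Conclusion.** The point holds as one about control, not about a particular error rate. As written, the provision permits an efficacy stop on an observed effect alone, while the design and final test assume one look at one-sided 5%. That level is not guaranteed, and the estimate at such a stop would be too favourable to the boost.

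The overall error could be close to 5% (crude difference, first used from year 4) or about 55% (hazard ratio below 0.675 from year 1, no minimum number of events), with yearly 0.05 tests at about 20%. These figures assume exponential failure and loss, no delay in detecting failure by PSA, reviews at whole years from the start of accrual, and a board that always stops when the criterion is met. The last assumption makes them upper values for each reading. The matter should be settled before the board acts on recurrence data by arm.

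**What to change.** Replace the efficacy sentence with a pre-specified conservative group-sequential boundary. Either of these would do:

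- Haybittle-Peto: consider an efficacy stop only if the one-sided log-rank p is below 0.001 and a minimum number of failures has occurred, for example 80 (half of the roughly 160 required). On the planning assumptions the first yearly review to reach 80 would be about year 6 (64 failures expected at year 5, 97 at year 6). The final test stays at one-sided 5%. Overall error is about 5.3% without the minimum, and the minimum can only lower it.
- An O'Brien-Fleming-type boundary over the same looks, with the final critical value moved to about 1.78.

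The choice between them is secondary. In either case, send the board Kaplan-Meier estimates and the log-rank statistic for efficacy, and say that a stop under the boundary is what meets the requirement of significant superiority.

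The cost is one paragraph in the protocol or board charter. Haybittle-Peto loses no power because the final test is unchanged; O'Brien-Fleming costs about one to two percentage points (81% to 79%). No extra patients are needed for the first option. The real downside is a lower chance of an early efficacy stop.
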